### Randomization

Each CNLBP participant will be randomized to a general exercise group or a core stabilization exercise group with a ratio of 1:1. Randomization will be performed using a block-balanced randomization technique with 4 character blocks containing letters A and B. After randomizing, the randomization schedule will be transferred into written instructions and will be placed in sequentially numbered, opaque, sealed envelopes. The CNLBP participant will be blinded to which intervention group they are in until the end of the study. The procedure will be performed by an investigator who will not be involved with participant assessment, allocation, or treatment. The randomization schedule is known only to a physical therapist who treats the patients. The male physical therapist ([name]) assessing participants before and after the treatment will also be blinded to group allocation, and the patients will be asked not to disclose this to the physical therapist.

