In this study, we will try to balance some of most important prognostic indicators of LBP such as educational status, smoking, working status, age, gender, and pain intensity in 2 treatment groups [27,28]. This strategy will help minimize the effects of confounding variables. Participants who do not complete the treatment sessions (absence for 3 consecutive or a total of 5 sessions) will be excluded from the study. Before participation in this study, procedure of this investigation will be explained both verbally and in writing, and written informed consent will be obtained from all participants. In addition, the participants will be assured that their personal information will be kept confidential (confidentiality principle). Participants will be identified only by initials and participant number on the research notes. All study results and completed questionnaires will be anonymized. All trial documents will be stored securely and not accessible to people outside of the research team. Participants will be withdrawn from this investigation if there are any concerns regarding informed consent.

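### The Randomization section contradicts itself on who knows the allocation schedule, and the balance aim and participant blinding lack support in the text

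*Protocol article*

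**What the plan says.** All references are to the protocol article.

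- **Randomization, sequence.** Patients are allocated "with a ratio of 1:1" by a "block-balanced randomization technique with 4 character blocks containing letters A and B". No other block size is given.
- **Randomization, custody.** The schedule is turned into written instructions that "will be placed in sequentially numbered, opaque, sealed envelopes". The article adds: "The procedure will be performed by an investigator who will not be involved with participant assessment, allocation, or treatment". The next sentence reads: "The randomization schedule is known only to a physical therapist who treats the patients".
- **Randomization, blinding.** "The CNLBP participant will be blinded to which intervention group they are in until the end of the study". The assessing therapist is also to be blinded, and "the patients will be asked not to disclose this to the physical therapist". Study Design and Ethics labels the trial double-blind.
- **Participants.** The authors write that "we will try to balance some of most important prognostic indicators of LBP such as educational status, smoking, working status, age, gender, and pain intensity", and describe this as a strategy against confounding.
- **Statistical Analysis.** The two treated arms are compared by a mixed ANOVA whose only factors are group and time.

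**The concern.** Randomisation protects the comparison only if nobody who can influence who enters, or when, can foresee the next assignment. Read literally, the custody sentence gives the upcoming list to a person in contact with patients and makes the envelopes redundant for that person.

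The balance aim raises a related problem. It names patient characteristics that the described sequence does not use, so the reader cannot tell how it would be pursued. Staff could be left to improvise.

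The blinding text is in tension with itself. A patient who does not know the group has nothing to disclose. If patients do know or can work it out, self-reported pain (VAS) and disability (RMDQ) are open to expectation effects that a blinded assessor cannot remove.

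The randomised comparison has only 30 patients, so a few steered allocations would matter.

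**Working it through.** The article gives no figure on this point to reproduce. The check sets the statements side by side and then calculates what fixed blocks of 4 imply.

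**1. Custody.** I read the procedure as generating the list and filling the envelopes.
- Statement A: an investigator outside assessment, allocation and treatment does this. That person must therefore know the schedule.
- Statement B: only the treating therapist knows the schedule.
- A and B cannot both be literally true. Under B, the envelopes of statement A conceal nothing from the therapist, who would know 100% of assignments in advance.

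**2. Predictability if custody is corrected.** Inputs are block size 4 and ratio 1:1 (Randomization) and 30 randomised patients (Participants). The Examiners section has one therapist treating the CNLBP patients, so that person sees every past assignment. The block size is published. There are 6 equally likely orders of AABB.

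| Position in block | P(assignment is certain) | P(best guess is right) |
|---|---|---|
| 1 | 0 | 1/2 |
| 2 | 0 | 2/3 |
| 3 | 1/3 (first two alike) | 1/3 × 1 + 2/3 × 1/2 = 2/3 |
| 4 | 1 | 1 |
| Mean | (4/3)/4 = 33.3% | 2.833/4 = 70.8% |

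Thirty patients make 7 full blocks plus 2. Expected certain assignments are 7 × 4/3 = 9.3. Expected correct guesses are 7 × 2.833 + 1/2 + 2/3 = 21.0 of 30, against 15 by pure chance.

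**3. Balance.** Permuted A/B blocks balance arm counts only. The six named factors, each made binary, would form 2^6 = 64 cells, or 30/64 = 0.47 patients per cell, so stratifying on all of them is not workable.

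To show what chance leaves, take one binary factor with 9, 12 or 15 of the 30 patients positive (prevalence 30%, 40% or 50%, assumed). With 15 per arm, the hypergeometric probability of a gap of at least 5 patients (33 percentage points) is:
- 30%: 0.109
- 40%: 0.060
- 50%: 0.143

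For at least one of six such factors, assumed independent, 1 − (1 − p)^6 gives 0.50, 0.31 and 0.60. This is ordinary chance imbalance, not bias. It shows only that the stated aim is not met by the stated method.

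The ANOVA does not fill the gap. It uses each outcome's own pre-treatment value, so baseline pain enters the pain analysis, but none of the other named factors enters any analysis described.

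**4. Blinding.** Patients are said to be unaware of their group, yet are asked to keep it from the assessor. The exercise sections describe different programmes, demonstrated and supervised, with target muscle activation of about 30% in one arm and 60% to 70% in the other. Patients can at least describe what they do. The Equipment section calls the RMDQ self-administered, and pain is a VAS rating, so the patient is the source of both measurements.

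**The case against.** Several points on the other side have force.

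- **Concealment has not been shown to fail.** A reader might infer that the therapist will foresee every assignment and that concealment is absent. The article does not support this. It does not say that the therapist recruits, judges eligibility or opens envelopes. Recruitment is by advertisement and physician referral, a different and blinded therapist does the assessment, and Initial Assessment places randomisation after it. The custody sentence may mean only that the therapist learns each assignment in order to deliver it. This stands as a limit on the conclusion. It does not remove the contradiction, because the text speaks of the schedule and names nobody as opening envelopes.
- **Fixed blocks of 4 are not an error in themselves.** This also stands. Predictability matters only if the person who can guess also influences entry. The possible 16:14 split (probability 2/6 from the last two patients) is trivial.
- **The balance statement is an aim, not a promise.** The wording is tentative and the factors are examples. A reader might infer that staff will override the sequence, but nothing describes that. A reader might also calculate that at least one of six factors will differ by more than 0.5 SD with probability 68%: 2 × [1 − Φ(0.5/√(2/15))] = 0.171 each, and 1 − 0.829^6 = 0.675. The arithmetic is right, but it assumes six independent continuous factors. Education, smoking, working status and gender are categorical, and correlation among the factors is plausible.
- **Participant blinding is claimed.** A reader might infer that only the assessor is blinded, but the article says otherwise. Both arms are active exercise with the same warm-up, frequency and duration, and the core arm's last 6 sessions bring in exercises similar to the other arm's. Patients could be unaware of the group label. The main outcomes listed are kinematics and relative phase, so the doubt falls mainly on pain and disability.

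**Conclusion.** The concern holds in limited form, and the text should be changed.

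- **Custody:** a real contradiction within one section. Concealment is not assured for a person in contact with patients. Whether it would fail depends on the therapist's role at entry, which the article does not state.
- **Block size:** once custody is corrected, a therapist who sees past assignments still knows one third of assignments in full blocks for certain and guesses about 71% correctly. This assumes that the therapist knows the block size and the order of entry.
- **Balance:** the aim has no mechanism in the sequence or in the analysis described. The imbalance probabilities rest on assumed prevalences and independence.
- **Blinding:** the non-disclosure request undercuts the participant half of the double-blind label. Protection of pain and RMDQ is doubtful rather than disproved.

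**What to change.** 1. State that only the independent investigator holds the schedule, and name by role who opens the envelopes. Each numbered envelope is opened only after eligibility, consent and baseline assessment are complete. The order of assessment and randomisation is already planned; the opening rule needs to be explicit.
2. Use randomly varied block sizes and do not disclose them to treating or assessing staff.
3. Replace the intention to try to balance with one feasible method: stratification on a single factor such as baseline pain, or a prespecified baseline covariate adjustment. Say that the other factors will only be described.
4. Describe blinding by role: assessor blinded, treating therapist not blinded, participants at most unaware of the group label or the hypothesis. Do not rely on the double-blind label.

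The cost is a new envelope set and revised wording. No extra staff are needed, because the independent investigator is already in the plan. Slightly unequal arms are possible. With unstratified even blocks of up to 6, the worst split of 30 is 16:14, as now. With stratification the split can be somewhat wider, because stratum sizes are not known in advance and the last block in each stratum may be incomplete.

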### Examiners

Participants will be evaluated by a male physical therapist ([name]) who is a doctoral candidate with more than 6 years of clinical experience. In addition, CNLBP patients’ treatment will be performed by a female physical therapist who is a master’s degree student with more than 10 years of clinical experience in orthopedic physical therapy and certified in manual therapy.

### Equipment

Pain will be measured by the use of a 100 mm point VAS, and functional disability will be measured using the Persian translated version of the Ronald-Morris Disability Questionnaire (RMDQ). The RMDQ is a self–administered disability measure that was first published in 1983 [29]. It provides a tool for measuring the level of functional disability experienced by a patient suffering from LBP. The RMDQ includes 24 statements relating to the individual’s perceptions of their LBP and associated disability divided into 6 domains: physical ability and activity (15), sleep and rest (3), psychosocial (2), household management (2), eating (1), and pain frequency (1) [29]. The RMDQ is designed to take about 5 minutes to complete, without any assistance from the administrator. Validity and reliability of the Persian translated version of the RMDQ has been evaluated by Mousavi et al [30], who reported high correlation between the results of this questionnaire and the physical functioning scales of the Short Form Health Survey (*r*=–0.62) and excellent reliability (intraclass correlation coefficient =0.86). In addition, Mousavi et al [30] concluded that the Persian translated version of the RMDQ can measure functional status in Persian-speaking patients with LBP. The RMDQ has been selected for measuring functional disability because Parthan et al [8] stated that the RMDQ is the most responsive instrument and is recommended for clinical trials in CLBP.

STS and its reverse kinematic variables will be captured at a sample frequency of 100 Hz using good resolution (1.3 megapixel) cameras and a 3-dimensional motion capture system (Qualisys AB). Kinematic data will be analyzed using Qualisys track manager (QTM) software (Qualisys AB), MatLab version R2015b (MathWorks Inc), and Excel version 2016 (Microsoft Corp).

### Motion Capture System

A 3-dimentional approach will be used for data collection. However, only kinematic data in the sagittal plane will be used for analysis. According to Shum et al [12], motions out of the sagittal plane have insignificant amplitudes and cannot be used for analysis. A total of 6 Oqus 300 cameras (Qualisys AB) will be set up and angled in a manner to decrease hidden spots that might obscure data collection. In addition, the QTM software will be used to synchronize the 6 Oqus 300 cameras that record marker motion. The cameras identify infrared reflective markers which are attached to the participants and output 3-dimensional coordinates for each marker. Prior to testing, the motion system will be calibrated by recording an L-frame and dynamic movement of a T-wand for 60 seconds. After data collection, the markers will be labeled according to the anatomical landmark to which each marker is attached.

### Marker Setup

A total of 14 reflective markers will be placed on anatomical landmarks. Lumbar spine segment is modeled by placing 2 25.4 mm spherical markers on the T12 and S2 spinous processes [31]. The intercrestal [32] or intercristal line [33]—the line joining the superior aspect of the iliac crests posteriorly—will be used to find the L3 spinous process or L3-L4 spinal level [34,35]. Once the L3 spinous process or L3-L4 spinal level is identified, the physical therapist will palpate the spinous processes in the midline and trace them from inferior to superior to find the T12 spinous process. The posterior superior iliac spines (PSISs) line—the line joining the right and left PSISs—will also be used to find the S2 spinous process [34]. Furthermore, 4 14.0 mm spherical markers will be placed on the anterior superior iliac spines (ASISs) and PSISs of both sides to the define pelvis segment. In order to define femur segments, 8 14.0 mm spherical markers will be placed on the right and left greater trochanters, lateral femoral epicondyles, calcaneuses, and base of the 5th metatarsals. Markers will be placed by the same investigator ([name]) for all trials. Marker trajectories will be used to calculate the position and orientation of the anatomical frames of the 4 segments (pelvis, lumbar, and 2 hips). Sagittal lumbar angle is defined as the angle between the lumbar and pelvis segments. In addition, sagittal right hip (RH)/left hip (LH) angles are defined as the angle between the right and left femur and pelvis segments. The joint coordinate system [36] will be used to calculate sagittal joint angles.

### Procedure

#### Initial Assessment

After the recruitment process is complete and agreement to participate is obtained, participants will be brought into the biomechanics laboratory of the School of Rehabilitation Sciences, Iran University of Medical Sciences (Tehran, Iran). To ensure the activity is as natural as possible, few constraints will be placed on the procedure of STS movement and its reverse. Participants will not be allowed to use their hands to push up, and the feet should stay on the floor [12]. In order to standardize head posture and prevent the negative impact of the thoracic and cervical spines on lumbar spine kinematics, a visual target (white A4 paper with a black circle drawn upon it) will be adjusted to eye level in front of participants [31]. Data collection will begin with the capture of a reference standing posture. Then, participants will be asked to sit in their usual posture on an adjustable stool with neither armrest nor backrest. The stool provides support from the ischial tuberosities to the middle of the thighs. Foot placement will not be restricted and participants will be requested to relax their arms, hanging them next to their thighs. The stool height is 110% of knee-floor length, which is defined as the distance between the floor and the apex of the fibular head [12]. Participants will be instructed to stand up at their self-selected normal speed following a loud voice command (“Start”) and remain a comfortable and erect posture for 3 seconds. They will then be asked to sit down on the chair at their own comfortable speed and maintain this position for 3 seconds. Each subject will repeat the movements 3 times, and the mean data will be used for statistical analysis. Asymptomatic participants will serve as a control group in the first assessment in order to detect differences in kinematic parameters during STS and its reverse between the CNLBP patients and asymptomatic participants. Hence, they will not participate in the intervention phase and the second assessment (Figure 1).

Following the assessment, CNLBP participants will be randomly divided into 2 groups (core stabilization exercise and general exercise) for treatment. First, all CNLBP participants will perform warm-up exercises that consist of 8 stretching exercises (hamstrings, quadriceps, latissimus dorsi, and iliotibial band of both sides; 1 set of 5 repetitions with a 10-second hold per repetition) and stationary bicycling for a period of 10 minutes [37,38]. Based on the previous recommendations, a staged approach will be followed for both groups [38] (see Multimedia Appendix 1). This approach includes 8 exercise levels with progressively increasing difficulty [38]. In the first session, the exercises will be explained and demonstrated to CNLBP participants. We will try to use the Template for Intervention Description and Replication checklist [39] as a guideline to improve the completeness of reporting of our intervention procedure.

**Figure 1 figure1:**
[figure not shown]
CONSORT diagram illustrating flow of participants through the COSCIOUS.

#### Core Stabilization Exercise

Core stabilization or motor control exercise is a common type of therapeutic exercises prescribed for LBP patients. Core stabilization exercise is designed to re-educate the coactivation pattern of abdominals, paraspinals, gluteals, pelvic floor muscles, and diaphragm [23,40]. The biological rationale for core stabilization exercise is primarily based on the idea that the stability and control of the spine are altered in patients with LBP [41]. A core stabilization exercise program begins with recognition of the natural position of the spine (midrange between lumbar flexion and extension ROM), considered to be the position of balance and power for improving performance in various sports [42]. Initial low-level sustained isometric contraction of trunk stabilizing muscles and their progressive integration into functional tasks is the requirement of core stabilization exercise [21]. To ensure correct activation of the transversus abdominis muscle, it will be emphasized to CNLBP participants that the lower part of the anterior abdominal wall below the umbilical level needs to be “drawn in” during contraction of this muscle. Furthermore, bulging action of the multifidus muscle needs to be felt under the physical therapist’s fingers when they are placed on either side of the spinous processes of the L4 and L5 lumbar vertebral levels, directly over the belly of the muscle [37]. Participants will be made aware of and will be told to avoid incorrect muscle activation (substitution strategies).

#### General Exercise

General exercise is an umbrella term that can involve strengthening exercise for all the main muscle groups with or without the addition of weights [43]. In addition, this umbrella term can consist of exercises improving coordination, stretching, and aerobic fitness training [43]. In our study, exercises activating the extensor (paraspinals) and flexor (abdominals) muscle groups will be performed in a lying position initiating with simple movements and progressing to more difficult exercises (eg, on a gym ball).

The same frequency (*3 times per week*; Saturday, Monday, Wednesday) and duration (6 weeks; 16 sessions) will be provided for both groups [37]. All treatment sessions will be held in the morning (8 AM to 12 PM). In each session, participants will be instructed to perform their exercises as many times as they can with rest periods in the same session. However, the holding time and number of contractions will be progressively increased up to 10 contraction repetitions × 10 second duration each [38]. Finally, exercise sets will be increased from 3 to 5 sets. The first session will last for 30 to 45 minutes, and the time of treatment session will be gradually increased in a dose-dependent manner. Based on Koumantakis et al [38] study, CNLBP participants in the core stabilization exercise group will be asked to activate their muscles at about 30% of their maximum activation level during the performance of stabilization exercises, and CNLBP participants in the general exercise group will be asked to activate their muscles at about 60% to 70% during the performance of general exercises. However, in the core stabilization exercise group, heavier load functional tasks, with exercises similar to those conducted by CNLBP participants in the general exercise group, will be progressively introduced in the last 6 sessions of the program [37]. All exercises will be performed under supervision of an experienced physical therapist. Moreover, to control confounding variables and create a standard and homogeneous condition for all CNLBP participants, they will be instructed not to perform exercises at home between the treatment sessions. Treating physical therapist will explain the positive effects of exercise on health in each session to improve adherence of CNLBP participants to intervention protocol. Any deviations from the exercise protocol, such as the receipt of any additional interventions or therapy for LBP, will be recorded and the decision will be made on whether the participant should be excluded from the study.

After 16 treatment sessions, all CNLBP participants will be evaluated again in the same manner as the initial assessment. Pain intensity and functional disability will be measured using the VAS and the Persian translated version of the RMDQ. Figure 1 illustrates a Consolidated Standards of Reporting Trials (CONSORT) diagram of this study.

### Management of Adverse Events

CNLBP participants will be encouraged to contact their treating physical therapist between appointments if they have any concerns about their exercise program or if they experience an increase in pain. These concerns will be addressed by their treating physical therapist and details of the issue and outcome recorded [44]. Any adverse events will be recorded and reported to the ethics committee at Iran University of Medical Sciences.

